# Chinese herbal formula Xuefu Zhuyu for primary dysmenorrhea patients (CheruPDYS): a study protocol for a randomized placebo-controlled trial

**DOI:** 10.1186/s13063-021-05050-w

**Published:** 2021-01-26

**Keywords:** Chinese herbal medicine, Primary dysmenorrhea, Xuefu Zhuyu Oral Liquid, Placebo, Randomized controlled trial

## Abstract

**Background:**

Epidemiological studies have shown that young women often suffer from primary dysmenorrhea (PD) which is a common cause that affects their routine work and quality of life. Chinese herbal medicine has been widely used for PD in China. A systematic review found that Xuefu Zhuyu (XFZY) has a promising effect on PD management, yet there is a dearth of high-quality evidence in support of this claim. We want to conduct a randomized controlled trial to evaluate the efficacy and safety of XFZY for PD patients.

**Methods:**

This is a protocol for a multicenter, randomized, placebo-controlled trial. A total of 248 participants with PD will be recruited at 6 centers and randomized into two groups—a herbal treatment group and a placebo group. The participants will receive either XFZY or placebo, three times per day, for 3 menstrual cycles, with a 12-week follow-up. The primary outcome will be the mean change in pain intensity as measured by VAS, while the change in menstrual pain duration, the change in peak pain intensity as measured by VAS, the Cox Menstrual Symptom Scale (CMSS), quality of life EQ-5D-5L, cumulative painkiller consumption, and health economics will be included as secondary outcomes. Adverse events will also be reported.

**Discussion:**

This protocol describes a multicenter, double-blind, randomized, placebo-controlled trial that investigates the efficacy and safety of XFZY for primary dysmenorrhea. Validated evaluation tools will assess dysmenorrhea severity. We believe that this research will provide important evidence regarding the use of XFZY to treat dysmenorrhea.

**Trial registration:**

Chinese Clinical Trial Registry ChiCTR1900026819. Registered on 23 October 2019

## Background

Dysmenorrhea is a common gynecological disease. Its prevalence ranges from 50 to 90% across ethnicities and geographical locations [1]. Dysmenorrhea can be classified into primary dysmenorrhea (PD) and secondary dysmenorrhea, with the former more prevalent in young women [2]. More than one half of PD patients are moderate or severe among Chinese Female University students [3], diminishing young females’ quality of life [3, 4], restricting their daily activities, and causing absenteeism from work and school [3, 4]. Despite its high incidence, most patients do not seek medical help for dysmenorrhea [5].

Non-steroidal anti-inflammatory drugs (NSAIDs) are an effective treatment for PD [5, 6], but can cause adverse events in the gastrointestinal tract and central nervous system [7]. These include indigestion, headaches, and drowsiness [6]. Hormone therapy generally requires periodic, prolonged, or continuous use [5], and patients may find it inconvenient. Therefore, some patients also seek complementary and alternative therapies, including Chinese medicine (CM), to treat PD.

Physicians of Chinese medicine treat patients according to pattern differentiation. Pattern (*Zheng* or syndrome in Chinese medicine) is a diagnostic conclusion based on pathological changes in a disease at a certain stage. It includes features such as the nature of the disease, cause, location, and development trends [8]. *Qi stagnation* and *blood stasis pattern* (*QBP*) are common PD patterns [9–11]. Its features always present as distending pain and stabbing pain [12]. The CHM formula Xuefu Zhuyu (XFZY) has been widely used in clinical in China [13] and was the most frequently used in research focused on blood stasis in Korea [14]. It comes as both an oral liquid and a capsule [15]. XFZY promotes *Qi* and activates the *blood* to relieve *QBP* symptoms [12].

Pharmacological experiments have found that XFZY restrains platelet aggregation induced by adenosine diphosphate, arachidonic acid, and collagen [16]. This has been shown to inhibit thrombogenesis in rats [16, 17] and increase the number of open capillaries [18]. Thus, it can be inferred that XFZY can treat the pathogenesis of QBP.

XFZY was approved by the China Food and Drug Administration (CFDA) in 2002 [19] and has been included in the Chinese pharmacopeia [20]. XFZY’s components include Persicae semen (Taoren), Carthami flos (Honghua), Rehmanniae radix (Dihuang), Angelicae sinensis radix (Danggui), Chuanxiong rhizome (Chuanxiong), Paeoniaeradix rubra (Chishao), Achyranthis bidentatae radix (Niuxi), Platycodonis radix (Jiegeng), Bupleuri radix (Chaihu), Aurantii fructus (Zhiqiao) fried with bran, and Glycyrrhizae radix et rhizome (Gancao).

A recent systematic review [21] revealed that XFZY has a promising effect on PD management. Some trials also found the efficacy of XFZF on PD. For example, a randomized clinical trial (RCT) [22] found that XFZY had a higher cured rate and a lower recurrence rate compared with indomethacin for PD. Some other trials also found XFZY had a better response rate for PD as compared to conventional medication (e.g., diclofenac sodium, ibuprofen) with head-to-head comparison [23–25] or add-on design [26, 27]. Another randomized trial found that compared with fenbid solely, XFZY decoction plus fenbid had a better pain intensity relief [28]. But in the review [21], none of the included trials used a placebo as a control or with blinding of participants and personnel. Moreover, most of the previous trials appeared to be of low methodological quality. So far, XFZY’s efficacy lacks evidence from RCTs with rigorous methodology. Thus, we have designed a multicenter, participant- and personnel-blinded, randomized placebo-controlled trial to evaluate the efficacy and safety of XFZY for PD with *QBP*.

## Methods/design

### Aim

The aim is to evaluate the efficacy and safety of XFZY for PD patients with *QBP* in Chinese medicine (CM).

### Design and setting

This is a multicenter, randomized, placebo-controlled trial. It will be conducted in 6 university hospitals in different Chinese provinces. A flow chart of this trial is provided in Fig. 1. The trial consists of a treatment period of 3 menstrual cycles and a follow-up period of 3 menstrual cycles. After providing written informed consent, eligible patients will be randomized to receive either XFZY or placebo at a ratio of 1:1.

**Fig. 1 Fig1:**
[figure not shown]
Flow diagram. VAS, visual analog scale; CMSS, Cox Menstrual Symptom Scale; AEs, adverse events

The trial’s design and conduction will adhere to the Declaration of Helsinki and have been approved by the ethics committees at Guangdong Provincial Hospital of Chinese Medicine (No. BF2019-175-01) and each center. The trial was registered at the Chinese Clinical Trial Registry (No. ChiCTR1900026819) on 23 October 2019.

### Participants

#### Diagnostic criteria

##### PD diagnostic criteria

The diagnostic criteria for dysmenorrhea are based on primary dysmenorrhea consensus guidelines (2017) [5]. PD is characterized by crampy, suprapubic pain before or after the onset of menstrual bleeding. Its symptoms peak with maximum bleeding and may persist for 2–3 days. It is often accompanied by diarrhea, nausea and vomiting, fatigue, dizziness, headache, or even syncope and fever. In this RCT, abdominal ultrasound and gynecological examination will be conducted to exclude secondary dysmenorrhea and other causes of menstrual pain.

##### QBP diagnostic criteria

QBP diagnosis in CM is based on a scale which has been verified with validity and reliability [29]. Table 1 shows the symptoms and signs evaluated with the diagnostic scale.

**Table 1 Tab1:** CM syndrome diagnostic scale for QBP [12]

Symptoms/signs	Yes	No	Score
Pain	9	0	
Irritability/depression	16	0	
Distending pain	2	0	
Scurry pain	6	0	
Chest distress	0.5	0	
Lumps in body	7	0	
Petechia in the tongue	4	0	
Purplish tongue	1	0	
Unsmooth pulse	4	0	
Deep pulse	2	0	
Total score If ≥ 20 points, it is diagnosed as QBP			

Pain includes stomachache, abdominal pain, low back pain, dysmenorrhea, breast pain, limb pain, etc.

*CM* Chinese medicine, *QBP* Qi stagnation and blood stasis pattern

##### Inclusion criteria

The following are the inclusion criteria:
Meet the diagnostic criteria for PD and QBP in CMAged 18 to 35 yearsMenstrual cycle (21 to 35) daysPain visual analog scale (VAS) score > 4Signed informed consent

##### Exclusion criteria

The following are the exclusion criteria:
Secondary dysmenorrhea confirmed by gynecological ultrasound or caused by pelvic inflammation, endometriosis, cervix tumor, endometrial polyp, or other ailmentsSevere primary cardiovascular, liver, kidney, or blood disease; mental illness (schizophrenia, epilepsy, alcoholism, anorexia, and/or a history of serious mental illness and those taking antidepressants, antiserotonin, barbiturates, or psychotropic drugs); or other severe primary diseasesLactating and pregnant women or women who have recently been preparing for pregnancyAllergy to herbal ingredients in the studyParticipants in other clinical trialsThose who have been treated with hormone drugs over the last 3 monthsSelf-Rating Anxiety Scale (SAS) ≥ 60 or Self-Rating Depression Scale (SDS) > 62

### Recruitment

Recruitment advertisements will be posted on hospital notice boards and the WeChat (Shenzhen Tencent Computer System Co. Ltd., Guangdong, China) messaging client to recruit potential participants. Outpatient clinical staff will also screen and refer potential patients who will then access the study information. Interested PD patients can register for this trial by contacting researchers. Researchers will then arrange screening visits with potential participants 0–14 days before their onset of the next menstruation. Participants with PD will be enrolled at one of the following 6 hospitals in 4 different Chinese provinces: (1) Affiliated Hospital of Liaoning University of Traditional Chinese Medicine in Liaoning Province, (2) Guangdong Provincial Hospital of Chinese Medicine in Guangdong Province, (3) The Second Affiliated Hospital of Liaoning University of Traditional Chinese Medicine in Liaoning Province, (4) The First Affiliated Hospital of Heilongjiang University of Chinese Medicine in Heilongjiang Province, (5) The First Hospital of China Medical University in Liaoning Province, and (6) Affiliated Hospital of Inner Mongolia University for the Nationalities in Inner Mongolia Province. A signed consent form will be obtained from every participant who is eligible and willing to participate in the trial.

### Randomization and allocation concealment

A center-stratified and permuted block randomization sequence will be generated by SAS 9.2 (SAS Institute Inc., Cary, USA) and performed by the Institute of Basic Research in Clinical Medicine, China Academy of Chinese Medical Sciences (IBRCM). Eligible participants will be randomly allocated to either the XFZY group or the placebo group at a ratio of 1:1 through the Interactive Web Response System, developed by IBRCM. The randomization sequence will be strictly confidential and maintained by IBRCM. All participants, investigators, outcome assessors, statisticians, and other staff involved in this trial will have no chance to know the treatment allocation until the end of the study.

### Blinding

All participants, investigators, statisticians, pharmacists, and other staff will be blinded to the treatment assignments throughout the trial. The placebo will be identical to the XFZY in appearance, weight, taste, smell, and packaging. When serious adverse events (SAEs)/adverse reactions (SARs) occur or a subject’s condition deteriorates, and it is necessary to know their specific treatment so as to take emergency rescue, then blinding will be uncovered and participants and/or investigators will know the specific treatment. The reason, date, and results of the unblinding will be recorded in a case report form (CRF).

### Interventions

#### Experimental group

Participants in the experimental group will take XFZY orally three times per day (20 ml each dose) for 14 days before the onset of menstruation. The treatment period will last 3 menstrual cycles (XFZY will be administered for 14 days during each menstrual cycle). After treatment, there will be a 12-week follow-up.

The XFZY will be manufactured by Jilin Aodong Yanbian Pharmaceutical Co. Ltd. (Jilin Province, China) according to the requirements of the Good Manufacturing Practice (GMP). XFZY is composed of 11 herbs: peach kernel, safflower, *Rehmannia glutinosa*, ligusticum chuanxiong, red peony root, radix platycodonis, radix platycodonis, radix bupleurum, bran fried fructus aurantii, licorice, and *Angelica sinensis*.

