#### Control group

Patients in the control group will receive a placebo with no active ingredients, but consistent with XFZY in terms of dosage, appearance, smell, taste, and texture. It will also meet the hygiene inspection requirements. The placebo’s primary ingredients are honey, white granulated sugar, fried brown sugar, bitterants, ginseng essence, natural edible pigments, and food antiseptic. The placebo will also be taken orally (20 ml each dose) three times per day for 14 days before the onset of menstruation for 3 menstrual cycles. The placebo is also manufactured by Jilin Aodong Yanbian Pharmaceutical Co. Ltd. in line with the GMP requirements.

Both XFZY and the placebo will be labeled and packaged based on a randomization sequence by Jilin Aodong Yanbian Pharmaceutical Co. Ltd. under the supervision of IBRCM.

A box containing a 14-day dose of either XFZY or placebo will be distributed to subjects in the pharmacy department or clinic office every menstrual cycle, from visit 1 (menstrual cycle 1) to visit 4 (menstrual cycle 4).

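### The allergy exclusion covers only the herbal ingredients, so known allergy to a non-herbal placebo ingredient does not bar entry; separately, the herb list in the intervention section repeats one herb and omits another

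*Protocol article*

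**What the plan says.** Four places in the protocol article bear on this.

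- **Exclusion criteria.** The single allergy item is confined to the herbal ingredients used in the study. The other items concern secondary dysmenorrhea, severe somatic or mental illness, pregnancy and lactation, other trials, recent hormone treatment, and anxiety or depression scores.
- **Control group.** The placebo is matched to XFZY, and "The placebo’s primary ingredients are honey, white granulated sugar, fried brown sugar, bitterants, ginseng essence, natural edible pigments, and food antiseptic". It is taken in the same volume and on the same schedule as XFZY: 20 ml three times a day for 14 days before menstruation, over three cycles.
- **Experimental group.** The product is introduced with "XFZY is composed of 11 herbs: peach kernel, safflower", and the list goes on to "radix platycodonis, radix platycodonis, radix bupleurum, bran fried fructus aurantii, licorice", ending with Angelica.
- **Background.** The components of XFZY are given once each and include "Achyranthis bidentatae radix (Niuxi), Platycodonis radix (Jiegeng), Bupleuri radix (Chaihu".

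**The concern.** In a blinded two-arm trial nobody knows at screening which product a woman will receive, so she must be fit to take either one. An allergy exclusion therefore has to span the ingredients of both products. Here it is tied to herbs, while the placebo consists mainly of sweeteners, colouring, bittering agents and a preservative. A woman who reports a known allergy to one of these would meet no exclusion criterion. At stake is an avoidable exposure of a participant with a known contraindication.

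The herb list is a lesser matter. The section that defines the intervention contradicts its own count and differs from the Background. A reader who takes the composition from that section takes an incomplete one.

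**Working it through.** **1. Allergy criterion against the placebo list.** Each placebo ingredient under Control group is set against the wording under Exclusion criteria.

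| Placebo ingredient | Reached by a criterion limited to herbal ingredients? |
|---|---|
| Honey | No |
| White and brown sugar | No |
| Bitterants | Not on its wording |
| Edible pigments | Not on its wording |
| Food antiseptic | No |
| Ginseng essence | Arguably yes, as a herbal ingredient of the study |

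No inclusion criterion mentions allergy. None of the other exclusion items deals with allergy to an ingredient either.

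**2. Size of the exposure.** The inputs are 20 ml per dose, three doses a day, 14 days per cycle and three cycles (Control group), with 124 women planned per group (Sample size calculation).

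- Daily volume: 20 × 3 = 60 ml.
- Days of dosing: 14 × 3 = 42.
- Total volume: 60 × 42 = 2,520 ml per woman.
- With 1:1 allocation, an eligible woman with such an allergy has a one-in-two chance of receiving the placebo.

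These figures describe exposure, not risk. The document gives no frequency of allergy to any of these ingredients, so no expected number of reactions can be computed.

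**3. The two herb lists.** Latin and common names are matched to the same herb.

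| Background | Experimental group |
|---|---|
| Persicae semen | peach kernel |
| Carthami flos | safflower |
| Rehmanniae radix | Rehmannia |
| Angelicae sinensis radix | Angelica (listed last) |
| Chuanxiong | chuanxiong |
| Paeoniae radix rubra | red peony root |
| Achyranthis bidentatae radix | **absent** |
| Platycodonis radix | platycodon, **twice** |
| Bupleuri radix | bupleurum |
| Aurantii fructus | fructus aurantii |
| Glycyrrhizae radix | licorice |

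- Background: 11 entries, 11 distinct herbs.
- Experimental group: 11 entries, 10 distinct herbs, against a stated count of 11.
- In Background only: Achyranthes. In Experimental group only: none.

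In the Background, Achyranthes stands between red peony and platycodon. In the Experimental group list, the first of the two platycodon entries stands in that place. Putting Achyranthes there gives 11 distinct herbs, the same set as in the Background.

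**The case against.** The strongest reply on the allergy criterion is that the protocol nowhere calls honey, pigments or preservatives allergens and gives no prevalence. That is right. The point rests on the assumption that some women know they are allergic to such an ingredient, and it sets no figure on how many. It also stands that clinicians may ask about allergies anyway, although the written criterion does not require it. The protocol has other safeguards: emergency unblinding, withdrawal at any time, active enquiry about adverse events, and 24-hour reporting of serious ones. All of these act after the woman has been exposed, so they do not close a gap at screening.

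Four stronger readings are tempting, and the document does not support them.

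- A reader might infer that two different formulas are under test. Every herb in the shorter list is in the longer one, the stated count agrees with the longer one, and the duplicate sits where the missing herb belongs. This is a copying slip. The article also describes XFZY as an approved pharmacopeia product made under GMP, so the slip gives no reason to doubt what is in the bottle.
- A reader might infer that sites would fail to ask about Achyranthes. Nothing tells sites to screen from the intervention section, and the full list is in the same article.
- A reader might infer that reactions to placebo ingredients would distort the comparison of adverse events. No frequency is given. Nor does the document say whether XFZY liquid contains similar non-herbal ingredients, in which case such reactions need not fall on one arm.
- A reader might see ginseng essence as contradicting the claim that the placebo is inactive. Whether it is only a flavouring is a specification detail that an article can leave to the full protocol, and no contradiction is shown.

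**Conclusion.** The allergy criterion is drawn too narrowly. As written, it lets in a woman with a known allergy to a non-herbal placebo ingredient and exposes her, with probability one half, to 60 ml a day of a liquid containing it. This follows from the wording alone. The number of women concerned is unknown and probably small, so this is a worthwhile low-cost improvement and not a serious defect of the design.

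The herb list is a clerical error: one of 11 entries is a duplicate standing in for Achyranthes. The two points are independent, and correcting the list would leave the allergy gap open. Neither is shown to touch the sample size, the primary analysis or the safety comparison.

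**What to change.** Reword the exclusion to: allergy to any ingredient of XFZY or of the placebo. Screening staff then need the full ingredient list of both products, which can be supplied without revealing allocation.

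The cost is a minor protocol amendment, in a trial approved by the ethics committees of the lead hospital and of each center, and the loss of a few otherwise eligible women. According to the Trial status section, recruitment began in January 2020 and was still open, with completion expected in March 2021. The change would therefore protect only those not yet enrolled.

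In the Experimental group section, replace one of the two platycodon entries with Achyranthis bidentatae radix (Niuxi), after checking the manufacturer's specification, so that the list agrees with the Background and with its own count of 11. This is a text correction only.

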#### Control group

Patients in the control group will receive a placebo with no active ingredients, but consistent with XFZY in terms of dosage, appearance, smell, taste, and texture. It will also meet the hygiene inspection requirements. The placebo’s primary ingredients are honey, white granulated sugar, fried brown sugar, bitterants, ginseng essence, natural edible pigments, and food antiseptic. The placebo will also be taken orally (20 ml each dose) three times per day for 14 days before the onset of menstruation for 3 menstrual cycles. The placebo is also manufactured by Jilin Aodong Yanbian Pharmaceutical Co. Ltd. in line with the GMP requirements.

Both XFZY and the placebo will be labeled and packaged based on a randomization sequence by Jilin Aodong Yanbian Pharmaceutical Co. Ltd. under the supervision of IBRCM.

A box containing a 14-day dose of either XFZY or placebo will be distributed to subjects in the pharmacy department or clinic office every menstrual cycle, from visit 1 (menstrual cycle 1) to visit 4 (menstrual cycle 4).

#### Discontinuing interventions

Participants will be free to withdraw from this clinical study at any time and for any reason. The reasons and time for discontinuing will be recorded on CRFs, reported, and analyzed. Subjects will be terminated from the trial if the following conditions occur: (1) PD aggravates and progresses aggressively during the treatment period and investigators decide the patient needs to withdraw; (2) during the research period severe systemic disease such as an active malignant tumor, decompensated cirrhosis, or hematopoietic systems diseases are found; (3) surgery is needed due to acute abdomen, trauma, or other diseases during the treatment period; (4) voluntary withdrawal from the trial; or (5) serious complications occur, and treatment is needed.

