#### Primary outcome

The primary outcome is change in the mean pain intensity as measured by the visual analog scale (VAS), from baseline to the end of treatment. The VAS rates the severity of menstrual pain from 0 to 10 cm (no pain to the most serious pain imaginable) [30]. Participants will self-rate their mean pain intensity using VAS at baseline and each visit.

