### Statistical analysis

Data will be processed with PASW Statistics 18.0 (IBM SPSS Inc., Armonk, New York, USA) and SAS (SAS Institute Inc., Cary, USA). Statistical analysis will be performed by qualified statisticians who are independent from the research team and are blinded to treatment allocation. Two-tailed *P* values < 0.05 will be considered statistically significant. The analysis will be based on the intent-to-treat (ITT) and the per-protocol (PP) principle. The ITT population will include all participants randomized to this trial. The PP population will only include participants with neither major protocol deviations nor low compliance. Missing data will be replaced in accordance with the principle of multiple imputations. There is no plan for any interim analysis. Efficacy assessment will be analyzed by ITT and PP population, simultaneously. If these two results are inconsistent, the ITT analysis will be considered the primary result.

Demographic and other baseline data will be presented by descriptive statistics. An independent *t* test will compare the change in the mean pain intensity as measured by VAS from baseline to the end of the treatment, between the two groups’ primary outcomes. Superiority will be confirmed by 95% confidence intervals. For secondary outcomes, continuous and categorical data will be compared between the two groups with either a *t* test, chi-square test or Fisher’s exact test. Frequency, mean, standard deviation (SD), median, and range of secondary outcomes will be summarized. To analyze the factors affecting the outcome change at each time point, either a mixed-effects or a linear or logistic regression model will be performed adjusting for baseline characteristics such as age, menstrual pain severity, cumulative painkiller consumption, and other variables. The repeated measure analysis of variance will be conducted to distinguish the treatment effect and time effects. Subgroup analysis will be performed based on disease severity and age.

Safety will be assessed by AEs and ADRs and will be presented with descriptive statistics for each group. Frequency differences for AEs and ADRs will be compared with a chi-square test or Fisher’s exact test.

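### Participants withdrawn for aggressive worsening leave the trial, not only study medication, so an endpoint lost because of its own course is then imputed

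*Protocol article*

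**What the plan says.** The protocol article, Discontinuing interventions, opens its list with "Subjects will be terminated from the trial if the following conditions occur: (1) PD aggravates and progresses aggressively during the treatment period". Criterion (1) in full is "PD aggravates and progresses aggressively during the treatment period and investigators decide the patient needs to withdraw". Criteria (2), (3) and (5) cover severe systemic disease, surgery, and serious complications that need treatment. Voluntary withdrawal is a separate item, (4). On recording, the section says only: "The reasons and time for discontinuing will be recorded on CRFs, reported, and analyzed". It does not say whether outcomes are collected afterwards.

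The section Primary outcome defines the endpoint as follows: "The primary outcome is change in the mean pain intensity as measured by the visual analog scale (VAS), from baseline to the end of treatment". On timing it adds: "Participants will self-rate their mean pain intensity using VAS at baseline and each visit".

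Under Statistical analysis: "The ITT population will include all participants randomized to this trial", and "Missing data will be replaced in accordance with the principle of multiple imputations". The imputation sentence makes no distinction by reason for missingness. If the intent-to-treat and per-protocol results disagree, the intent-to-treat result is the primary one.

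**The concern.** The section heading is about stopping the intervention, but the rule ends participation in the trial. Its natural reading is that VAS ratings stop as well. Because voluntary withdrawal has its own item, people removed under the other criteria have not withdrawn consent, and their outcomes could still be obtained.

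Criterion (1) turns on the course of menstrual pain, which is what the primary outcome measures. Ordinary multiple imputation assumes that, given the observed data, missingness does not depend on the unseen value. Where the deterioration that led to removal is not in a recorded VAS, that assumption fails and the imputed change is too favourable for that arm.

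The per-protocol analysis is a weak check. It excludes major deviations and low compliance, so it will often leave out the same people (an inference, since the article does not say so).

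At stake is whether an intent-to-treat analysis of everyone randomized rests on observed outcomes for the participants who did worst.

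**Working it through.** **Inputs.** Sample size calculation gives assumed changes (improvement, in cm) of 3.0 (SD 0.94) on XFZY and 0.88 (SD 1.64) on placebo, a difference of 2.12. The article gives no expected number of criterion (1) removals and no imputation model, so the shares removed and their true change are assumptions below.

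**The plan's own figure.** With an average SD of √((0.94² + 1.64²)/2) = 1.337, one-sided α of 0.025, power 0.80 and a difference of 2.12 − 1.6 = 0.52, the normal formula gives 104 per group and the unequal-variance t version gives 105. Then 105/0.85 = 123.5, so 124. The stated 105 and 124 reproduce, but only if 1.6 is treated as a superiority margin. The article calls it an MCID, so the bias is not scaled against 0.52 here.

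**Formula.** If removed participants have true mean change c and are imputed near their arm mean, each arm mean is too high by the share removed times the gap between imputed and true change:

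bias in the difference = pX(3.0 − c) − pP(0.88 − c).

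With c = −1 this is 4.0·pX − 1.88·pP:

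| pX | pP | Bias (cm) |
|---|---|---|
| 5% | 5% | 0.200 − 0.094 = +0.11 |
| 1% | 5% | 0.040 − 0.094 = −0.05 |
| 0% | 5% | 0 − 0.094 = −0.09 |

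At equal shares c cancels and the bias is 2.12p in favour of XFZY: 0.11 cm at 5% and 0.21 cm at 10%. The sign changes once placebo removals exceed 4.0/1.88 = 2.1 times those on XFZY (c = −1), or 4.82/2.70 = 1.8 times (c = −1.82).

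**Which split fits the protocol's figures.** Taking the changes as normal:
- Worse than baseline: z = −3.0/0.94 = −3.19, about 0.07% on XFZY; z = −0.88/1.64 = −0.54, about 30% on placebo.
- Worse by more than 1 cm: z = −4.0/0.94 = −4.26, about 0.001%; z = −1.88/1.64 = −1.15, about 13%.

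These ratios are far beyond 2.1, which puts the bias against XFZY.

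**Effect of earlier ratings.** A simulation used 200,000 per arm, the protocol's means and SDs, three cycles, correlation 0.6, a linear build-up of effect, and removal when worse than baseline by more than 1 cm. The placebo arm's true mean is 0.88.
- Worsening recorded at cycle 1 or 2 before removal (29% of placebo removed): imputation from the person's own earlier VAS gives 0.92; draws from those who stayed, ignoring earlier VAS, give 1.38.
- Worsening at cycle 3 with no rating (13% removed): 1.13 and 1.26. Those removed have a true mean of −1.82 and are imputed at 0.17 and 1.25.

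The XFZY mean stays at 3.00 to 3.02 because few are removed. In the unrecorded case the difference falls from 2.12 to 3.00 − 1.13 = 1.87 or 3.00 − 1.26 = 1.74. The 1-cm threshold is a device of the simulation, not the protocol's rule.

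**The case against.** The strongest reply has four parts.

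First, criterion (1) is narrow. It needs aggressive progression and an investigator's decision, and Rescue and concomitant treatment provides painkillers for unbearable pain without removal. Few may be affected. This stands: the point concerns some participants, not everyone whose pain worsens. Criterion (5) is not defined by pain either, so outcome-dependent loss is argued for criterion (1) only.

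Second, VAS is rated at every visit, so the deterioration may already be on record. This also stands. A reader might infer that the worst results are simply replaced by those of people who stayed, but that is literally true only if the imputation ignores earlier ratings, and the article does not say that it does.

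Third, the imputation model and missing-data sensitivity analyses usually belong in an analysis plan, which is not shown. Their absence from the article is therefore no defect. However, whether VAS is collected after medication stops is a rule of conduct set here, and no analysis plan can recover values that were never collected.

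Fourth, the section does not expressly forbid later ratings, and the schedule in Table 2 is not shown. That leaves room for a kinder reading, but ending participation in the trial is hard to square with continued visits.

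**Conclusion.** The point holds in limited form. Discontinuing interventions does not separate stopping study medication from leaving the trial. Under criterion (1) the endpoint is lost for a reason tied to the endpoint, and the primary analysis then imputes it.

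The size cannot be fixed from the documents, because the share removed is unknown. In the scenarios above, the placebo mean is overstated by 0.04 cm when worsening is recorded and used, and by 0.25 to 0.38 cm when it goes unrecorded and 13% are removed.

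A reader might infer that the bias favours XFZY. The documents do not support that: it needs removals on XFZY to be at least about half of those on placebo (1.88/4.0 = 47% at c = −1), whereas the protocol's own means and SDs put worsening almost wholly on placebo. That in turn rests on normality and on the assumed XFZY effect being true. If XFZY works less well than assumed, the shares move closer together and the direction is open. The sound conclusion is a bias of unknown sign that could not be checked afterwards without the data.

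**What to change.** Leave the clinical criteria as they are. In Discontinuing interventions, distinguish stopping study medication from leaving the trial. For criteria (1), (2), (3) and (5), continue collecting VAS, CMSS, painkiller use and EQ-5D-5L at the visits already scheduled for each, unless consent is withdrawn, and use the observed values in the intent-to-treat analysis.

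Where the endpoint is still missing after a criterion (1) withdrawal, include the person's earlier VAS values in the imputation. Add one prespecified sensitivity analysis that drops the missing-at-random assumption, for example imputing the baseline VAS (no improvement) or a delta adjustment.

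The cost is amendment wording, a few follow-up contacts and one extra analysis. Trial status says recruitment was under way, so further data collection helps only those who can still be followed. For anyone whose endpoint is already lost, only the analysis steps remain.
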